## **Introduction**

Headache and pain symptoms related to neck and shoulders are a clinical challenge, as well as a major health problem.

Therapeutic exercise proved to be able to decrease the intensity of pain in the neck-shoulder area (Konijemberg et al., 2001; Ylinen et al., 2003), also in the workplace, but in a few studies, with different methodological approaches, which do not allow a proper comparison of the results.

Muscle tenderness, above all of pericranial muscles, whose pathophysiological role has been widely proved in tension-type headache (Langemark and Olesen, 1987; Jensen et al., 1998), has recently come into question also in migraine as a factor affecting the disease natural history, above all in relation to psychiatric comorbidity (Mongini et al., 2004). Therefore, relieving muscle tenderness by physical exercise is expected to ameliorate also the headache. Recently, in a small sample of office workers, a positive effect of a workplace physical exercise intervention has been preliminarily demonstrated on the intensity either of the neck and shoulder symptoms, or of the headache, in a cluster randomized controlled cross-over study (Sjögren et al., 2005).

Subjects suffering from different headache types usually complain of numerous accompanying symptoms, behavioural and somatic, which may be partially related to psychiatric comorbidity (Maizels and Burchette, 2004), in particular to anxiety and mood disorders, which are common in this population. The relationship between headache and depression or anxiety disorders seems to be bi-directional (Merikangas et al., 1993; Breslau et al., 2003; Zwart et al., 2003). From recent evidence, physical exercise seems to yield an antidepressant efficacy (Ernst et al., 2006; Harris et al., 2006; De Moor et al., 2006).

Many studies were performed to assess the efficacy of non invasive physical interventions in the treatment of different types of headache and cervical pain. Dynamic muscle training and relaxation training are often prescribed for chronic neck pain. However the evidence on their effectiveness is still limited and the results of recent studies are conflicting (Ylinen J et al., 2003; Viljanen M et al., 2003; Sjogren T et al., 2005).

Meta-analyses show that the clinical effectiveness of non-invasive physical treatments for headache and neck pain require further research using scientifically rigorous methods (Borghouts JA et al., 1998; Kjellman GV et al., 1999; Gross AR et al., 2000; Gross AR et al., 2000; Bronfort G et al., 2001; Linton SJ et al., 2001).

In this complex interplay among muscle tension, headache, neck-shoulder pain and psychiatric comorbidity, so as to achieve a better understanding of the role of physical exercise in relieving pain symptoms, longitudinal, controlled studies are required, in which a precise diagnostic categorization of the subjects not only for the headache type, but also for the psychiatric comorbidity is mandatory. In a previous non-randomized-controlled study in which the cognitive and physical programme was applied to a consistent number of office workers, a significant reduction of frequency of pain in the head and neck areas and of analgesic drug consumption was obtained. The present study was designed to confirm the data in a much more extensive working population and applying a randomised design.

### **Primary objective**

- To confirm the effectiveness of a workplace cognitive and physical programme (Intervention), in reducing the frequency of pain involving the head and neck area in a large working community using a randomized design.

### **Secondary objectives**

- To confirm the effectiveness of the Intervention, in reducing the intensity of pain involving the head and neck area in a large working community using a randomized design.
- To confirm the reduction in analgesic drugs consumption after the Intervention in a large working community using a randomized design.
- To evaluate the persistence of the effectiveness of the Intervention after 12 months in a large working community using a randomized design.

### **Study design**

This is a controlled, cluster randomised, interventional trial conducted on the local government employees of the Municipality of Turin. The participants will be distributed in two groups according to local departments distribution. The eligible source population consists of 11780 workers in 444 departments. A cluster-randomised design will be employed to assign the eligible population in two groups (study and control group) stratified for professional groups and number of participants.

## **Primary outcome**

The primary outcome measures are:

- the headache frequency
- the neck and shoulder pain frequency.

The efficacy of the Intervention will be measured in two ways:

- a) responders rate. End-point: proportion of subjects with more than 4 days with headache (neck and shoulder pain) during the baseline period that will have reduction in pain frequency of more than 50%, after 6 months.
- b) reduction in the frequency of pain. End-point: number of days per month with a headache (neck and shoulders pain), after 6 months.

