### **Sample size**

Of the eligible 11.780 workers, we will expect a participation rate of 20% of the sample.

The planned 2356 subjects (half per group) will provide a power of 0.95 to detect at least a difference of 10% ( $\alpha = 0.05$ , two-tails) in the proportion of symptomatic subjects (more than 4 days with pain during the baseline) that will have a significative reduction of pain frequency (assuming a prevalence of symptomatic subjects of 50%, a significative reduction ( $\geq 50\%$ ) in 20% of subjects in the Intervention group, a significative reduction in 10% of subjects in the Control group, and taking into account the cluster-randomized design of the study, assuming an intracluster correlation  $\rho = 0.15$ ).

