### **Statistical analysis**

Subjects who will not give informed consent or will not complete the baseline diary (month 1) will be excluded from the analysis. The data will be analysed according to group distribution.

The **principal analysis** will be conducted between intervention and control group for the first phase of the study (months 1-7; Figure 1, line 1).

Analyses will be performed on subjects for which diaries will be completed for months 1 and 7.

The proportion of subjects with more than 50% reduction in headache days (and in neck and shoulder pain days) at the end of the study period will be assessed and compared between the two groups accounting for the cluster-randomized design of the study.

For each subject, the difference (Delta) in the frequency of symptoms between months 7 and the baseline (month 1) will be calculated; the Deltas between the two groups will be compared with parametric and non-parametric tests, where appropriate, taking into account the cluster-randomized design of the study.

Possible baseline differences between the study group and the controls will be evaluated with parametric and non-parametric tests where appropriate; unbalanced factors will be taken into account in the analysis, if necessary.

Explorative subgroup analyses will be performed by age, gender, severity, compliance, diagnosis, and type of job activity.

A **secondary analysis** (Figure 1, line 2) will be conducted within the intervention group, in order to evaluate the persistence of the efficacy of the intervention; the frequency of pain at months 13 will be compared with that observed at months 7.

A further secondary analysis will be conducted in order to compare the efficacy of the program in the intervention group (end of phase 1) and in control group (end of phase 2).

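### Four unranked primary endpoints sit under one confirmatory objective with no success rule, while the only alpha and power belong to one responder comparison of an unnamed pain

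*Protocol*

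**What the plan says.** The Primary objective section of the protocol states one confirmatory aim: "To confirm the effectiveness of a workplace cognitive and physical programme (Intervention), in reducing the frequency of pain involving the head and neck area".

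The Primary outcome section lists two primary measures, headache frequency and "the neck and shoulder pain frequency". It adds "The efficacy of the Intervention will be measured in two ways" and gives each way its own end-point at 6 months: the responder proportion, and the number of days per month with pain. Two pains by two measures makes four primary endpoints.

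The Statistical analysis section puts both kinds of comparison in the principal analysis. For responders it names both pains: "The proportion of subjects with more than 50% reduction in headache days (and in neck and shoulder pain days". For change in frequency it speaks of symptoms in general: "the Deltas between the two groups will be compared with parametric and non-parametric tests, where appropriate". It gives no order, no significance level and no criterion for success.

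Alpha appears once, in the Sample size section, as 0.05 two-tailed. The same sentence says "The planned 2356 subjects (half per group) will provide a power of 0.95 to detect at least a difference of 10" percent "in the proportion of symptomatic subjects (more than 4 days with pain during the baseline") who have a marked reduction. It does not say whether the pain is headache or neck and shoulder pain. It gives no standard deviation or expected difference for days per month.

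**The concern.** A confirmatory objective needs a rule that turns the primary results into a yes or a no. Here the results could split: headache could succeed and neck pain fail, or days could succeed and responder rates fail. The protocol does not say whether either pattern confirms the objective.

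The two headline figures, alpha 0.05 and power 0.95, cannot both describe that decision. If one success is enough, the overall error exceeds 0.05. If all must succeed, 0.95 is not the chance of success. A rule chosen after the results are known by group would carry little weight.

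**Working it through.** **Inputs from the protocol.** 2356 participants, half per group; 50% symptomatic; responder rates 20% and 10%; intracluster correlation 0.15; alpha 0.05 two-sided (Sample size). 444 departments (Study design).

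**Assumptions, not in the protocol.** Mean cluster size is not stated, so I take 2356/444 = 5.31 participants per department. The correlations between the four test statistics are not stated either.

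**1. Reproduce the stated power.**
- Symptomatic per group: 1178 × 0.5 = 589.
- Design effect: 1 + (5.31 − 1) × 0.15 = 1.646.
- Effective n per group: 589/1.646 = 357.8.
- Standard error under the null: √(2 × 0.15 × 0.85/357.8) = 0.0267. Under the alternative: √((0.16 + 0.09)/357.8) = 0.0264.
- Power: Φ[(0.10 − 1.960 × 0.0267)/0.0264] = Φ(1.80) = 0.964, or 0.955 with a continuity correction.

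The stated 0.95 is therefore sound for one responder comparison.

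**2. Error if any one of four tests at 0.05 counted as success.**
- Independent tests: 1 − 0.95⁴ = 0.185, which is 3.7 times 0.05. The upper bound is 4 × 0.05 = 0.20.
- Correlated tests, by simulation of four normal statistics (2,000,000 draws; the correlation across both pain and measure is the product of the two):

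| Between measures | Between pains | Either direction | Favouring intervention only |
|---|---|---|---|
| 0.3 | 0.3 | 0.177 | 0.090 |
| 0.5 | 0.5 | 0.161 | 0.081 |
| 0.7 | 0.5 | 0.149 | 0.074 |
| 0.8 | 0.7 | 0.128 | 0.064 |

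The reference level is 0.05 for the third column and 0.025 for the fourth. The inflation is about 2.6 to 3.6 times in both.

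**3. Power if all four had to succeed.** Suppose each test had power 0.95. Joint power is then at least 1 − 4 × 0.05 = 0.80, is 0.95⁴ = 0.815 if the tests are independent, and is at most 0.95.

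**4. Responder power at the strictest Holm step, 0.05/4 = 0.0125 (critical value 2.498).**
- Φ[(0.10 − 2.498 × 0.0267)/0.0264] = Φ(1.26) = 0.896, against 0.964 at 0.05.
- If only symptomatic participants count towards cluster size (1178/444 = 2.65, design effect 1.248), power is 0.966, against 0.991 at 0.05.
- If the stated 0.95 is taken as exact, Φ(1.960 + 1.645 − 2.498) = Φ(1.107) = 0.866.
- To keep 0.95 at alpha 0.0125 with design effect 1.646, about 2864 participants are needed, against 2166 at alpha 0.05.

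The same step cannot be done for the days-per-month tests, because the protocol gives neither a standard deviation nor an expected difference.

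**The case against.** The strongest reply is that the protocol nowhere says each test is run at 0.05, or that any one success suffices. A reader might infer both, because 0.05 is the only alpha given, and conclude that the error rate as planned is about three times nominal. The text does not support that. It states no rule, and under an all-must-succeed rule there would be no inflation. The threefold figure also rests on correlations that are not in the protocol. This part of the reply stands, so the error figures are conditional.

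Second, the objective is directional, so significant results in favour of control would not confirm it. That stands too. Counting only errors that favour the intervention, the rate is about 0.06 to 0.09. The fair comparator is then 0.025, so the multiple hardly changes, although set against 0.05 it is only about 1.3 to 1.8.

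Third, allocation of alpha is often left to a statistical analysis plan, and one may exist that is not shown. The absence of an alpha split is therefore not the point in itself. What remains is in the protocol's own text: four unranked primary endpoints, one objective, and a sample size that treats the primary question as a single responder test without naming the pain.

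Finally, a reader might take the 0.95 power to be wrong. It is not; it reproduces for the test it describes.

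**Conclusion.** The protocol sets its primary decision badly. It has four co-listed primary endpoints, one confirmatory claim and no statement of which results would establish it. On either natural reading, one headline figure fails to describe the trial:

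- **Any one of four at 0.05:** familywise error 0.185 if independent, and about 0.13 to 0.18 under assumed correlations of 0.3 to 0.8.
- **All four:** error is controlled, but joint power could be as low as about 0.80 even if every test had 0.95.

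The documents do not choose between these readings, so neither figure is the trial's actual error rate or power. The stated power is correct for one responder comparison of an unnamed pain. The days-per-month endpoints have no power statement and, on the information given, cannot have one.

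**What to change.** Add one paragraph, settled before month-7 results are compared between groups:

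- Apply the Holm procedure across the four primary tests at overall two-sided 0.05. Alternatively, test in a fully ordered sequence, each at 0.05, stopping at the first failure. The sequence must also rank the two pains within each measure; placing responder rates before days leaves two responder tests tied at the first step, and error stays uncontrolled there.
- Claim effectiveness only for the endpoints that pass.
- State which pain the responder rates, prevalence and power refer to.
- If Holm is used, restate responder power at alpha 0.0125.
- Give a standard deviation and expected difference for days per month, so that power can be stated for those tests.

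**Cost.** On the protocol's inputs, with an assumed 5.3 participants per department, Holm lowers worst-step responder power from 0.964 to about 0.90. This is before diary dropout, which the sample size does not allow for although the analysis uses only participants with diaries for months 1 and 7. No extra participants are needed if that loss is accepted; holding 0.95 would take about 2864 instead of 2356. An ordered sequence leaves the first test's power unchanged, but each later test depends on those before it. The cost for the days-per-month tests cannot be quantified from the protocol.

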## **Secondary outcomes**

Secondary outcome measures are:

- the headache index (Intensity x Frequency) after 6 and 12 months, where intensity is the sum of intensity of the daily pain in a month divided by number of days with headache and frequency is number of days with headache in a month.

Further secondary outcome measures are:

- the frequency of analgesic drug consumption after 6 and 12 months
- the frequency of headache (neck and shoulder pain) after 12 months

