## Schedule

After informed consent, all participants will be asked to submit data relative to the presence and characteristics of headache and neck and shoulder pain (September 2007), and to keep a diary (web-based) for one month (October 2007, baseline period).

The participants will be randomized (cluster-randomization) in two groups (study and control group) according to departments distribution (September-October 2007).

At month 2 (November 2007) an instruction program will be administered to the study group only. The intervention consists of brief shoulder and neck exercises to be performed several times a day, a relaxation exercise and instructions of how to reduce hyperfunction of the craniofacial and cervical muscles during the day (see: Intervention).

The control group, instead, will not receive any cognitive program.

Both groups will again fill in the diary during month 7 (April 2008).

At beginning of month 8 (May 2008, beginning of the second phase of the study), the same instruction program (Intervention) will be administered to the control group.

Both groups will again fill in the diaries during month 13 (October 2008, end of the study).

The study design according to time flow is reported in Fig.1

[figure not shown]

Fig.1 . Study design

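### Pain frequency is a raw count over diary months of 31, 30 and 31 days, which biases the secondary month 13 comparisons slightly towards apparent loss of effect

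*Protocol*

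**What the plan says.** Under Primary outcome, the second efficacy measure is "number of days per month with a headache (neck and shoulders pain), after 6 months", and a responder is a subject with more than 4 pain days at baseline "that will have reduction in pain frequency of more than 50%, after 6 months". Secondary outcomes uses the same scale for the headache index: "frequency is number of days with headache in a month". None of these definitions divides by the number of days observed or sets a standard month length.

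Schedule fixes the recording windows as calendar months. Participants are asked "to keep a diary (web-based) for one month (October 2007, baseline period"), then "Both groups will again fill in the diary during month 7 (April 2008"), and finally "Both groups will again fill in the diaries during month 13 (October 2008, end of the study").

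Statistical analysis makes the between-arm contrast over months 1 to 7 the principal analysis, in subjects whose "diaries will be completed for months 1 and 7". For persistence, within the intervention group only, "the frequency of pain at months 13 will be compared with that observed at months 7". A further secondary analysis sets the programme's efficacy in the intervention group at the end of phase 1 against that in the control group at the end of phase 2.

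**The concern.** A count of pain days depends on how many days were available to count. October has one more day than April, so a person whose daily risk of pain never changes is expected to record slightly more pain days at month 13 than at month 7.

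A comparison between arms in the same month absorbs this. A comparison between months does not, and two of the planned secondary analyses are of that kind. Persistence after 12 months is a named secondary objective. It has no concurrent untreated comparator, because the control group receives the programme from month 8. The artefact always points the same way, towards a fading effect, and the sample is large enough for a small shift to raise the false-positive rate noticeably.

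**Working it through.** **The plan's own figure.** The only checkable figure is the power of 0.95 under Sample size. Symptomatic subjects per arm: 2356 × 0.5 / 2 = 589. Mean cluster size: 2356 / 444 = 5.31. Design effect: 1 + (5.31 − 1) × 0.15 = 1.646. Effective number per arm: 589 / 1.646 = 357.8. Power for 20% against 10%, two-sided 5%: 0.964. This agrees with the stated 0.95 and is not in dispute. It is used here only for the design effect of about 1.65.

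**Size of the artefact.** Let p be an unchanged daily risk of pain.
- Expected pain days: 31p at month 1, 30p at month 7, 31p at month 13.
- Month 13 minus month 7 = p, which is 1/30 = 3.3% of the month 7 value.
- For month 7 means of 3, 5 and 8 days (assumed), this is 3/30 = 0.10, 5/30 = 0.17 and 8/30 = 0.27 days.

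**Cross-phase comparison.** If each group's effect is its change over its own phase, the artefact is 30p − 31p = −p in the intervention group (phase 1) and 31p − 30p = +p in the control group (phase 2). The two add to 2p, in favour of the intervention group's phase. If the month 7 and month 13 levels are compared instead, the artefact is p. The Protocol does not say which is meant.

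**Principal comparison.** With equal baseline risk, the between-arm difference in Deltas is 30 times the difference in month 7 daily risk, so there is no artefact. For an unchanged subject with 8 baseline days (p = 8/31), the binomial chance of fewer than 4 pain days at month 7 is 3.0% over 30 days and 2.5% over 31. That half-point shift is common to both arms.

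**Effect on a significance test of persistence.** Inputs that the Protocol does not give are assumed:
- Daily risk follows a beta distribution with first shape parameter 0.5, 1.2 or 4, and the second set so that half of subjects exceed 4 of 31 days (the plan's prevalence).
- SD of the within-person change is 2.7 to 5.8 days. The low end has no month-to-month variation in personal risk.
- n = 2356 / 2 = 1178 with no loss, or 825 (about 70% of 1178; the 70% is an assumption).

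The distributions give p = 0.23, 0.18 and 0.16 days, hence 2p = 0.47, 0.36 and 0.32. With z = p / (SD × √(DE / n)), the two-sided rejection probability is P(Z > 1.96 − z) + P(Z < −1.96 − z).

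| p | SD | n | z, DE 1 | Rejects | z, DE 1.65 | Rejects |
|---|---|---|---|---|---|---|
| 0.158 | 5.8 | 825 | 0.78 | 12% | 0.61 | 9% |
| 0.181 | 4.4 | 1178 | 1.42 | 29% | 1.10 | 20% |
| 0.233 | 2.74 | 1178 | 2.92 | 83% | 2.28 | 63% |

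A plain check without the beta model (mean 5, SD 5, n = 1178): 0.167 / (5 / √1178) = 1.14, which rejects in 21% of trials, or 14.5% with a design effect of 1.646.

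**Headache index.** Intensity is the month's summed pain score divided by pain days, and frequency is pain days. Their product is the summed score for the month, so it lacks a denominator in the same way.

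**The case against.** The strongest reply is that a 3.3% shift is small and secondary. The principal analysis is between arms over identical months. The Protocol says only that months 13 and 7 will be compared; it names no test for this and defines Delta only for months 7 and 1. A real or seasonal change could easily exceed a fraction of a day. With a larger SD or a smaller sample the false-positive rate comes close to nominal: a mean of 3, an SD of 6 and n = 589 give about 7%. All of this stands, and it sets the severity. It does not remove the artefact, which is in the estimate whatever test is used.

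Three stronger readings are tempting and are not supported.

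- **That the persistence analysis will show a false loss of effect.** It is biased in that direction. The 83% needs the most skewed distribution, no month-to-month variation in personal risk, no loss of subjects and no clustering.
- **That the primary endpoint is compromised.** The count is the primary scale, but month length nearly cancels where that scale is used for the principal contrast.
- **That blank diary days are counted as response.** Data collection asks for a daily entry of pain present or absent, so a pain-free day is itself an entry, and the analysis is limited to completed diaries. Nowhere does the Protocol say that blanks count as pain-free. How partly filled diaries are handled may be settled in an analysis plan that is not shown.

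**Conclusion.** The point holds as a minor one. As written, the plan puts a one-directional artefact of 3.3% (about 0.1 to 0.3 days) into the within-group month 13 versus month 7 comparison. In the cross-phase comparison the artefact is of the same size, or twice it if changes are compared. The month lengths and the direction follow from the Protocol alone. The absolute size in days rests on assumed means. The rejection rates (roughly 9% to 63% with a design effect of 1.65, 12% to 83% without) also rest on assumed SDs and numbers analysed, and on applying the plan's intracluster correlation to within-person changes. Sample size, stated power and the principal between-arm conclusion are not affected.

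**What to change.** Under Primary outcome, Secondary outcomes and Statistical analysis, define frequency as pain days divided by recorded diary days, times 30. Put the headache index on the same footing (summed score divided by recorded days, times 30). In a count model, an offset of log recorded days does the same job. Use this scale for the month 13 versus month 7 comparison and the cross-phase comparison, and state whether the latter compares changes or levels.

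The cost is one line per section and no new data, because the diary is kept daily. With full diaries the baseline threshold selects the same people: 5 days of 31 becomes 4.84 and 4 days becomes 3.87. The responder rule changes from c < b/2 to c < 30b/62 (b baseline days, c month 7 days), which alters the result only for b = 31 with c = 15.

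Two limits should be stated. If partly filled diaries are accepted, the scale would limit the effect of blank days, but it treats them as resembling filled days and needs a minimum number of recorded days beside it. It also does nothing about seasonal differences between April and October, so the persistence result should be reported with that caveat.
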